**Outcomes**

***Professional and familial situations***

Some questions are asked to collect information about the professional and familial situations of participants. We measure the level of schooling (Q. 6), diplomas obtained (Q. 7), the potential reasons of dropping out (Q. 8, 9 and 10), the adequacy of the professional formation to expectations (Q. 11) and professional projects (Q. 12). The question 19 asks about resources. The financial situation is also measured by asking the perception of the participant about his own financial situation (Q. 26), if he goes away for vacation during the last year (Q. 27) and if his household (Q. 28) or he has debt or credits (Q. 29).

The familial situation is also investigated by asking the marital status (Q. 15) and the composition of the household (Q. 16, Q.17). The question 18 asks the professional situation of the head of household. A special module (F) asks questions about the profession, nationality and the nature of relationship with both parents. It aims also at collecting information about childhood by questioning who was in charge of educating the participant (F. 10, 11, 12, 13), where the participant spent his childhood (F. 14, 15, 16) and if he lived difficult episodes during childhood and adolescence. The participant’s feeling about his own childhood and adolescence is also measured (F. 19, 20).

***Social environment***

A module (L) of the baseline questionnaire aims at describing the conditions of housing. Questions about the type of housing (L. 2), the rent (L. 3) and the perception of the accommodations (L. 5, L. 6) are asked.

The neighborhood is also investigated by the questionnaire. The main goal is to measure the reputation and perception of the living area (Q. 1 to Q. 7).

A short module (A) aims at collecting information on the level of social integration by asking participants about activities they practice or associations they are member of. This module is completed by a second one (R) about relations with peers which aims at giving an idea about the level of social integration of the participant. The number of friends (R. 1), the frequency of contacts (R. 2), the feeling about social integration (R. 5, 7) and the type of discrimination (R. 9, 10) the participant suffers from are measured. We try also to measure trust in institutions (R. 8).

***Self-reported health***

A part of our questionnaire aims at measuring self-reported health. Three initial questions are asked to know how the participant perceives his general health status (S. 1), his physical status (S. 2) and his psychological status (S. 3) in a scale with five possibilities (very good, good, medium, bad or very bad). The questionnaire asks if participants suffer from a chronic illness (S. 4), if it constitutes an obstacle in their everyday life (S. 5) and how participants perceive their own health in comparison to others (S. 7).

Three questions focus on weight by asking how others judge the participant’s weight (S. 28), how the participant perceives his own weight (S. 29) and if he would lose or win weight (S. 30). The possible financial strain for buying food is also measured (S. 27).

***Health care use***

Our measure of health care use is based on several questions. The first questions aim at measuring if participants have a regular doctor (S. 10, 11) and if they trust him (S. 12, 13). We examine whether participants use the public hospitals for non-emergency care (S. 14) and for which reasons (S. 15). We ask whether participants visit a GP during the last year (S. 16), others health professionals (S. 17) and specialists (S. 18).

***Access to care***

To assess whether participants have access to care, we ask first if the participant needed to give up medical care during the last year (S. 19) and if it is the case, for which reasons (S. 20) and for which care (S. 21). Two questions focus on dental care (S. 23, 24).

We include in these categories of outcomes questions about the type of health coverage (AD. 5, 6, 7 8.). However, we know that responses to this type of questions could be biased because of the lack of knowledge on the insurance system and the different types of Social Security *regimes*.

***Health knowledge***

Finally, the questionnaire aims at measuring the level of knowledge about three items: consequences of drugs consumption, sexuality and the health insurance system.

- 1. **Medical questionnaire**

This questionnaire is designed by health professionals among the study team. GP’s will fill in this survey during their consultations with participants. We design a medical questionnaire for two main reasons. Doctors are more qualified to collect objective information about health status. Moreover, for ethics questions, some very specific questions about health or health behaviors need to be asked by health professionals who are able to answer to health demand.

- 1. **Endline questionnaire**

***Professional and familial situations***

Some questions are asked to collect information about the professional and familial situations of participants. The familial situation is investigated by asking the composition of the household (Q. 1, Q.2). The question 3 asks the professional situation of the head of household. The question 4 asks about resources.

We measure professional projects (Q. 5) and the evolution of the chance to find a job soon compared to last year. The question 9 asks if the participant have worked in the last year, when was it, was it a full or a part-time job, how many weeks in total, with which kind of contracts (Q. 10-16). Questions 18 to 20 ak if the participants has participated to training sessions, which kind, how many sessions, and how many days. The question 21 asks if the participant has seen the working counsellor.

***Social environment***

Questions R1 to R6 aims at collecting information on the level of social integration by asking participants about activities they practice or associations they are member of. The number of friends (R. 7), the frequency of contacts (R. 8), the feeling about social integration (R. 9-13). We try also to measure trust in institutions (R. 14).

***Self-reported health***

A part of our questionnaire aims at measuring self-reported health. Three initial questions are asked to know how the participant perceives his general health status (S. 1), his physical status (S. 2) and his psychological status (S. 3) in a scale with five possibilities (very good, good, medium, bad or very bad). The questionnaire asks if participants suffer from a chronic illness (S. 4), opinions about the health care system (S. 5, S. 6) and how participants perceive their own health in comparison to others (S. 7). Two questions focus on what partcipants do in order to maintain their health (S. 8, S. 9).

***Health care use***

Our measure of health care use is based on several questions. The first question aims at measuring if participants have a regular doctor (S. 10) and if they trust him (S. 11, 12). We examine whether participants use the public hospitals for non-emergency care (S. 13) and for which reasons (S. 14). Questions S. 15 and S. 16 ask the participant if he went at least once in the ER and for which reason. We ask whether participants visit a GP during the last year (S. 17), others health professionals (S. 18) and specialists (S. 19), dentists (S. 28)

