However, others argue that eliminating financial barriers to health care is not an efficient solution to reduce disparities in health status. In a study conducted in Canada, Dunlop et al. (2000) show that people less educated and with lower income use physicians' services at a lower rate that those with higher income and level of schooling despite the existence of an universal health care system. Health insurance coverage is not sufficient to reduce disparities in health between socioeconomic groups (Adler et al., 1993). In the RAND health insurance experiment, Manning et al. (1987) do not find effects from a better insurance coverage on health outcomes. Universal coverage do not succeed in eliminating socioeconomic disparities in health status.

This study, conducted in five Missions locales, aims at testing the efficiency of two programs. Both interventions target young unskilled people from 18 to 25 years old. The first intervention aims to optimize health coverage in order to reduce or eliminate financial barriers to health access. A social worker is in charge of finding the most advantageous coverage, assisting young people during their administrative processing and providing information on the French public health and private insurance systems. The second treatment consists on a double intervention. The first part is the same as the one described as the first intervention. But it is completed with medical consultations. Indeed, participants randomized in this group are encouraged to visit the health professionals of the structure. During these visits, GP's and psychologists are in charge of providing information on the health care system and health, doing a global health check-up and sending participants to a specialist if need be.

This randomized experiment aims at measuring the impact of the two interventions over a 12-month period. It focuses on the impact on health demand and access but also on social integration and employment.

1. **Outcomes**
   1. **. Primary outcome**

To assess impact of health issue and its screening on professional training and social autonomy of unemployed youth.

- 1. **. Secondary outcomes**

Description of health outcomes and prevention knowledge of this population aged 18 to 25 years old

To improve the content and the frequency of social and preventive medical consultations

1. **Design**
   1. **Type of study**

It will be a parallel unmasked randomised parallel interventional study.

- 1. **Participants**

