***Participant identification***

Participants will be recruited among Missions locales.

5 Missions locales have been selected : Toulouse, Sénart, Clichy, Reims, Poitiers. These structures have been selected according to their interest for the study and their capacities of implementing the empirical design. Because one treatment consists of the intervention of health professionals, only *Missions locales* with a GP can take part in the study.

Any young people coming for the second time in the selected Missions Locales will be targeted in this study. Because more than a half of young people visit only one time the structure, we will select only those who will from a long-term counseling in order to reduce the attrition bias.

After finishing their meeting with their counselor, young people will go to the member of the field staff who will present the study design.

The randomization and inclusion in the study will run during one year. Each participant will be followed up during one year after completing the baseline questionnaire.

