***Second intervention***

Participants randomized in the second treatment group benefit from the first intervention described above but, in addition, they are also encouraged to visit health professionals working in the *Missions locales*.

These consultations with the GP aim first at investigating the young's health status, his level of health services' use and sending him to specialist in case of need. If the first appointment is systematic, participants are free to decide the frequency of the next consultations. The main goal of this second treatment is to encourage health-related behaviors among young adults by giving useful advices, increase comfort with the health care system and their belief in its capacity to satisfy their expectations.

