***Control group***

Participants in the control group benefit from the normal program offered by the *Mission locale* as both experimental groups. They are not encouraged to meet health professionals or social workers. But in case of need, they can take an appointment with health professionals.

- 1. **Recruitment and training of field staff**

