***Health professionals***

The second treatment implies the interventions of health professionals. In order to reduce the cost of interventions, we select only *Missions locales* which already employ doctors and psychologists. Psychologists accept to participate in two sites (Toulouse and Sénart). A meeting with GP’s will be organized. Because each GP has his one practice of medicine, the first objective, as for social workers, will be to harmonize the content of their interventions. GP’s will also be in charge of a part of the data collection by filling in a medical questionnaire. In fact, some information about participants’ health status will be directly collected by health professionals during the consultation. Doctors will be trained on the medical questionnaire.

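### As described, the endline GP-visit item (S. 17) also counts the Mission locale GP consultation that is itself the second intervention, so part of any arm 2 excess on this item is built in

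*Protocol*

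**What the plan says.** In the Protocol, Endline questionnaire, Health care use: "Our measure of health care use is based on several questions". One of them is the item at issue: "We ask whether participants visit a GP during the last year (S. 17), others health professionals (S. 18"). No place of visit is mentioned, and the Mission locale doctor is not excluded.

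Under Second intervention, arm 2 receives the social-worker intervention of arm 1 and then, "in addition, they are also encouraged to visit health professionals working in the" Missions locales. On the GP consultations the same section says: "If the first appointment is systematic, participants are free to decide the frequency of the next consultations".

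Under Control group, participants get no such prompt: "But in case of need, they can take an appointment with health professionals".

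On timing, Participant identification says: "Each participant will be followed up during one year after completing the baseline questionnaire". On psychologists, the Health professionals section says: "Psychologists accept to participate in two sites (Toulouse and Sénart").

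The purpose these items serve is given at the end of the Background: "It focuses on the impact on health demand and access but also on social integration and employment". The stated primary outcome is a different one (professional training and social autonomy), and the sample size rests on training attendance.

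**The concern.** The event that S. 17 asks about and the event that arm 2 delivers are the same kind of event: seeing a GP. The intervention follows baseline, and follow-up lasts as long as the recall period, so the arm 2 appointment normally falls inside the year that S. 17 covers. A participant who attends it and sees no other doctor can truthfully answer yes. A control with identical use of ordinary care would answer no.

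Delivery of the treatment can thus be read as its effect. At stake is the interpretation of one health-care-use item in the comparisons of arm 2 with control and of arm 2 with arm 1, which has no GP component. A difference on S. 17 could not show whether arm 2 led young people to use ordinary care more.

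**Working it through.** **The plan's own figure.** The protocol states no figure for GP visits. Its sample size is reproduced here only to obtain the number per arm. Inputs from the Sample size section: 55% against 65%, one-sided alpha 0.05, power 90%, dropout 15%.

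n = [1.645·√(2·0.60·0.40) + 1.282·√(0.55·0.45 + 0.65·0.35)]² / 0.10² ≈ 409.2, so 409 (410 if rounded up). Then 409/0.85 = 481.2 and 3 × 481 = 1443. The stated figures reproduce.

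**The built-in excess.** Let
- b = share who see a GP outside the Mission locale in the year, taken as equal in all arms (no effect on ordinary care);
- u = share of arm 2 who see the Mission locale GP;
- c = share of controls who see the Mission locale GP.

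The documents give none of these; all values below are assumptions. If inside and outside visits are independent:
- S. 17 yes in arm 2: b + (1-b)u
- S. 17 yes in control: b + (1-b)c
- Difference: (1-b)(u-c)

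For the comparison with arm 1, c is replaced by arm 1's use of the Mission locale GP.

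| b | u | c | Built-in excess |
|---|---|---|---|
| 0.9 | 0.25 | 0 | 0.1 × 0.25 = 2.5 points |
| 0.9 | 0.5 | 0 | 0.1 × 0.5 = 5 points |
| 0.8 | 0.5 | 0 | 0.2 × 0.5 = 10 points |
| 0.7 | 0.5 | 0.2 | 0.3 × 0.3 = 9 points |
| 0.7 | 0.7 | 0.2 | 0.3 × 0.5 = 15 points |
| 0.7 | 0.7 | 0 | 0.3 × 0.7 = 21 points |
| 0.6 | 0.9 | 0 | 0.4 × 0.9 = 36 points |

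**Chance of a significant result with no effect on outside care.** With 409 per arm, one-sided 0.05 and c = 0: 0.35 at 2.5 points (b = 0.9, u = 0.25); 0.86 at 5 points (b = 0.9, u = 0.5); 0.99 at 10 points (b = 0.8, u = 0.5).

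**If independence fails.** With c = 0, the excess is the share of arm 2 who see the Mission locale GP and no other. Given b and u, it lies between max(0, u-b) and min(u, 1-b). At b = u = 0.7 that is 0 to 30 points, against 21 under independence. It is larger if attenders are mainly those without another doctor, and smaller if they are mainly those who see a GP anyway.

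**Can other data remove it?** The GPs' medical questionnaire could show who attended. The endline section on the Mission locale doctor is described as covering satisfaction and the good and bad points of the consultation. Neither shows whether an attender also saw a GP elsewhere. For attenders, a single yes to S. 17 carries no information about ordinary care, so no later analysis recovers it from these sources.

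**The case against.** The strongest objection is that the questionnaire is not shown. The protocol gives a one-line summary of S. 17, and endline items S. 20 to S. 22, S. 29 and S. 30 are not described at all. One of them may ask where a visit took place, or S. 17 may already exclude the Mission locale. This stands, and it limits the point to the item as described.

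Two further objections concern size and remedy. Controls may book the same GP, which shrinks the excess; the term c allows for this, and an excess remains whenever u exceeds c. Total GP contact is also a legitimate measure of health demand, and later visits in arm 2 are the participant's own choice. Counting only outside visits would make a participant who replaces an outside GP with the Mission locale GP look like a fall in care. This stands too, and it is why outside visits should not be the sole outcome.

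A reader might infer more than the text supports:
- That S. 18 also rises by construction. Only the GP appointment is called systematic, and psychologists take part at two of five sites. S. 18 may be affected there; no more can be said.
- That health care use as a whole cannot be evaluated. The measure also covers having a regular doctor, trust, hospital and emergency use, specialists and dentists, most of which a Mission locale GP visit does not mechanically change. Specialist visits after referral are a genuine downstream effect.
- That the main comparison is compromised. GP visits are in neither the stated primary nor the stated secondary outcomes.

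**Conclusion.** The point holds for one item. As described, S. 17 mixes delivery of the second intervention with its effect on ordinary care, and arm 2 will tend to exceed control and arm 1 on it even without any change in outside care. S. 18 possibly has the same overlap at Toulouse and Sénart. The built-in excess is about 2.5 to 36 points over the assumed values, with 15 points at b = 0.7, u = 0.7, c = 0.2. This rests on assumed b, u and c, on independence of inside and outside visits, and on the arm 2 appointment falling within the recalled year; an interview held late could put it outside. The excess is small if nearly everyone sees a GP anyway and disappears if controls use the Mission locale GP as often as arm 2 does. The primary outcome and the sample size of 481 per group are not affected.

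**What to change.** Before the items are fielded, split endline S. 17 and S. 18, and the matching baseline items S. 16 and S. 17, into visits inside and visits outside the Mission locale. Then:
- use outside visits to judge the effect on ordinary care;
- show total visits alongside, so that substitution of one GP for another is visible;
- report inside visits in all three arms as uptake or use of the Mission locale service, not as an effect of arm 2. Control visits are allowed by the protocol and should be reported as such.

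If the questionnaire already excludes Mission locale visits, one sentence saying so in the endline Health care use section is enough.

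The cost is one extra sub-question per item. Sample size and visit schedule do not change.

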***Access to care***

To assess whether participants have access to care, we ask first if the participant needed to give up medical care during the last year (S. 24) and if it is the case, for which reasons (S. 25) and for which care (S. 26, S. 27). Two questions focus on dental care (S. 23, 24).

We include in these categories of outcomes questions about the type of health coverage (S31 to S37).

***Health knowledge and information***

The first questions of this section are about health information i.e. interest of the participant in health. information, feeling to be informed about different subjects (alcohol, tobacco, cannabis, birth control, STD, AIDS, pollution, food, vaccines, cancer and depression), where to get the information, to have searched in the last year some information in health (C. 1-C. 4). Then questions investigate about the French health system (C. 5, C. 6, C. 8, C. 9, C. 10).

Question C. 7 asks to the participant to answer if some affirmations about morning after-pill are correct or not. Questions C. 11, C. 12 and C. 13 are about sexual intercourse, type of birth-control used during the last sexual intercourse and the provider of the birth-control.

***Satisfaction of the consultation with the doctor in the ML***

The question of this section aims at investigate the level of satisfaction of the medical consultation, the positive and negative aspects of this consultation.

***Satisfaction of the meeting with the social worker in the ML***

The question of this section aims at investigate the level of satisfaction of the meeting with the social worker, the positive and negative aspects of this meeting.

**Beck hopelessness scale**

To finish, we ask all the items of the hopelessness scale to calculate a score that predicts a suicide risk.

1. Data collection, validation, capture and archivage

Data will be collected in a face-to-face questionnaire by research assistant. In each Mission Locale, a person will be chosen for the study monitoring (recruitment, follow-up, lost-to-follow up, late, …). All the data will be informatically captured on an Excel file. After recruitment, all participants will have a number randomly attributed by an alogrithm. The correspondence between numbers and names of participants will be kept by the research assistant and the doctor on a paper (but not on computers). On computer, the data will be only registered with the number of the participant. All the analyses will present only agregated results. The computers that will be used for the data captures won’t be the sames that are used in Missions Locales and will be locked by a personnal password.

All the questionnaires will be kept under key in the office of [name] (located in the Faculté de médecine Pierre et Marie Curie [name]) for 15 years and will be available for the study responsibles and the promotor of the study.

All the scientific publications will have to be authorized by the scientific responsible, [name].

1. Ethics

This study will be conducted according to the last update version (Edimbourg) de la Déclaration d'Helsinki, the recommandations in ethics and good practice in epidemiology adopted in 1999 by l'Association des Epidémiologistes de Langue Française [ADELF 1998], in its updated version of 2008. This protocol has a favourable advice of CNIL (Commission nationale informatique et libertés -number 1527880).

In each Mission locale, a poster will present the study.The signature of the informed consent will be receipt by the research assistant. This consent will remind the background and objectives of the study, the medical data that will be collected, the study duration, the individual beneficies of the study, and the referent person to apply the right to object or modification.

1. Study organisation

The steering committee will be composed of

- Equipe DS3 represented by [name] and [name]

- Mission locale de Sénart represented by [name], [name], [name]

- le CREST (centre de recherche en économie et statistique) represented by [name] [name] and [name].

